### Labelling and storage of IMP

The study medication (both PCC and Placebo (0.9% NaCl)) will be prepared and labelled as study medication for the PROTON trial conform GMP annex 13. The studymendication will be delivered and distributed freely by the Company to all participating centers.

#### Drug accountability

The local pharmacy in each participating centre is responsible for the correct storage and management of medication. All study medication (used, partially used and unused) will be noted on the provided Drug Accountability Form. The vials with remaining content will be disposed after usage, a signed record of all used study medication will be retained for inspection by the Monitor after completion of the trial. No study medication may be dispensed to any persons except to the subjects enrolled in the trial.

### Additional burden and risk associated with trial participation

Since PCC contains procoagulant proteins, there is a theoretical risk of thromboembolic complications associated with administration of this product.

PCC is manufactured from human plasma from living blood donors and thus the risk for viral transmittable disease cannot fully be excluded. The risk for transmittance is minimized by testing and screening the donor for past exposure to certain viruses. By testing donors for the presence of certain current viral infection, and by inactivation and elimination of certain viruses, the risk for transmission is further reduced. In this trial, to monitor viral safety of the PCC product, pre-treatment and post-treatment blood samples will be taken and stored until 1 year after the last patient is out of the trial.

There is a small risk for allergic or anaphylactic reaction to the study product PCC. In case of such an event, treatment with PCC will be ceased immediately. A severe anaphylactic reaction can lead to shock and can be life threatening. There is expertise in every participating centre to manage and treat such an event.

The following additional procedures will be performed in patients participating in the PROTON-trial:

– Prior to intervention, blood samples for viral safety check will be collected

– The intervention during induction of anesthesia consisting of receiving a intravenous dose of placebo or PCC.

– An extra plasma sample (together with routine lab) taken from the patient during 12 time points in the trial with regards to patient safety.

– A blinded INR measurement will be performed 30 minutes after intervention

– On day 3 and 7 Physical examination will be performed with special attention to clinical venous thromboembolic events.

– Extra electrocardiographic examination will be performed twice during the trial.

### Safety reporting

In accordance to section 10, subsection 1, of the WMO, the Investigator will inform the subjects and the reviewing accredited medical ethics committee (MEC) if anything occurs, on the basis of which it appears that the disadvantages of participation may be significantly greater than was foreseen in the research proposal. The trial will be suspended pending further review by the accredited MEC, except insofar as suspension would jeopardize the subjects health. The Investigator will take care that all subjects are kept informed.

#### DSMB

To ensure the safeguarding of the included patients and the expected additional burden with trial participation, a DSMB with independent experts has been installed. The advice(s) of the DSMB will be provided on a regular basis after receipt, review and analysis of the interim and final efficacy and safety data to the Sponsor and Investigators and to the MEC that approved the protocol.

#### Withdrawal of individual subjects

Subjects and Investigator can decide to terminate participation in this trial at any time for any reason, particular safety reasons, if they wish to do so without any consequences.

#### Premature termination of the trial

The trial will be terminated prematurely if we find a high rate of Serious Adverse Events in the PCC-group during the interim analysis, possibly liable to the study product.

#### (Serious- ) adverse events and suspected unexpected serious adverse reactions (SUSAR)

All adverse events (AE) will be recorded in the CRF.

Since orthotopic liver transplantation is a surgical procedure with significant morbidity and mortality, we will report serious adverse events (SAE) once every three months in line listing to all accredited MEC and the DSMB. SAE resulting in death and suspected unexpected serious adverse reactions (SUSAR) will be reported real time to the Sponsor. The Sponsor will notify all accredited MEC, the DSMB and the Competent Authorities (CA) if necessary.

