**Discussion:**

Patients with advanced cirrhosis have reduced plasma levels of both pro- and anticoagulant coagulation proteins. Prothrombin complex concentrate is a low-volume plasma product that contains both procoagulant and anticoagulant proteins and transfusion will not affect the volume status prior to the surgical procedure. We hypothesize that administration of prothrombin complex concentrate will result in a reduction of perioperative blood loss and transfusion requirements. Theoretically, the administration of prothrombin complex concentrate may be associated with a higher risk of thromboembolic complications. Therefore, thromboembolic complications are an important secondary endpoint and the occurrence of this type of complication will be closely monitored during the study.

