### Investigational medicinal product (IMP)

The study drug is PCC (Cofact®, Sanquin, The Netherlands) and the placebo is NaCl 0.9%. The known and potential risks of PCC are described in the summary of product characteristics (SPC). In this population, the theoretical risk for thromboembolic complications is a special point of care.

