### Endpoints

The primary endpoint will be the number of RBC units transfused during the OLT procedure and in the 24 hour post-surgery period, starting from arrival at the ICU. Other efficacy endpoints are (measured during surgery and during the 24-hour period post-surgery):

• The number of transfused units of fresh-frozen plasma

• The number of transfused units of platelet concentrate

• Fibrinogen concentrate administration

• Estimated blood loss

• Antifibrinolytic drugs

• Crystalloids or colloids administered

• Other escape medication used

• Estimated ascites loss

Safety is a secondary endpoint, safety parameters recorded are:

• All (Serious) Adverse Events with special focus on thromboembolic events

• General and liver-specific laboratory parameters

• Lowest pH, Ca++, lactate, temperature (during and within the first 24 h after surgery)

• Troponin levels, ECG and hepatic vessel ultrasound results

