A potential side effect of PCC in patients with cirrhosis may be a higher risk of thromboembolic complications. Thromboembolic complications are not infrequent after OLT and when thrombosis occurs in one of the hepatic vessels, this may lead to graft loss. In addition, patients undergoing OLT are at increased risk of developing central venous thromboembolic complications such as intracardiac thrombosis or pulmonary embolism [43]. The PCC we are going to use in our study is commercially available under the product name Cofact®. The efficacy and safety of Cofac® has been evaluated in several clinical studies and so far there has been no indication of an increased risk of tromboembolic events in participating patients [42,44-46]. However, most of these trials have been conducted in patients using vitamin K antagonists. There has been no trial reporting the use of Cofact® in cirrhotic patients. With regards to the nature of the product, the disturbed hemostasis in cirrhotic patients and the hemostatic disturbances caused by the OLT, we decided that thromboembolic complications will be an important secondary and safety endpoint in this trial.

For our primary endpoint we have chosen the number of transfused units of RBC. Blood loss will be registered as well, but should be considered as less stable parameter as blood loss will be mixed with ongoing loss of ascites.

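### A non-fatal serious thromboembolic event that is not judged a SUSAR can wait up to three months before the DSMB sees it; it should join the real-time reporting category.

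*Protocol article*

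**What the plan says.** The section of the protocol article on (serious) adverse events and SUSARs sets two reporting routes.

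- **Periodic.** Because liver transplantation itself carries much morbidity and mortality, "we will report serious adverse events (SAE) once every three months in line listing to all accredited MEC and the DSMB".
- **Real time.** "SAE resulting in death and suspected unexpected serious adverse reactions (SUSAR) will be reported real time to the Sponsor". Onward notification follows: "The Sponsor will notify all accredited MEC, the DSMB and the Competent Authorities (CA) if necessary". No time limit is given for that step.

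Elsewhere the article gives thromboembolism special standing.

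- Abstract, Discussion: "the occurrence of this type of complication will be closely monitored during the study".
- Investigational medicinal product: "In this population, the theoretical risk for thromboembolic complications is a special point of care".
- Endpoints, first safety parameter: "All (Serious) Adverse Events with special focus on thromboembolic events".
- Main Discussion: "when thrombosis occurs in one of the hepatic vessels, this may lead to graft loss". The same section names thromboembolic complications as an important safety endpoint and notes that no trial has reported on this product in cirrhotic patients.

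**The concern.** The reason given for quarterly listings, high background morbidity, is sound for SAEs in general. Expediting every serious event after a liver transplant would swamp the DSMB. The reason does not carry over to the one class of event that the article picks out as the plausible harm of the product. Under the stated rule, a non-fatal hepatic vessel thrombosis, intracardiac thrombus or pulmonary embolism goes into the same quarterly list as every other surgical SAE unless someone judges it a SUSAR.

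At stake is how soon the DSMB can look at individual cases. A cluster of non-fatal thromboses could build up between two listings while recruitment and dosing continue.

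**Working it through.** The article states no figure on this point, so the check is mainly of the text.

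**Step 1. Follow one event through the rule.** Take a non-fatal hepatic vessel thrombosis.

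1. It is not a death, so the first real-time criterion is not met.
2. If it is judged a SUSAR, it goes to the Sponsor in real time, and the DSMB is notified under the qualified wording quoted above. That qualifier may attach to all recipients or only to the competent authorities; the sentence can be read either way.
3. If it is not judged a SUSAR, it goes to the DSMB in the next three-monthly listing.

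**Step 2. Look for any other route to the DSMB.**

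| Section | What it provides | Faster route for this event? |
|---|---|---|
| DSMB | Regular advice, based on interim and final data | No |
| Interim analysis | One look, after 70 patients | No, except for an event just before the look |
| Premature termination of the trial | Stopping for a high SAE rate on PCC, at the interim analysis | No |
| Safety reporting | Informing the ethics committee and subjects, and suspension, if disadvantages may prove significantly greater than foreseen | Does not name the DSMB or a trigger event |

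The quarterly listing is therefore the earliest guaranteed route for branch 3.

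**Step 3. Separate detection from reporting.** Postoperative procedure and Additional study procedures call for hepatic vessel ultrasound within 24 hours and on days 3 and 7, troponin, ECG on days 3 and 7, targeted physical examination on days 3 and 7, and imaging on suspicion. Events should be found. None of these sections says when the DSMB hears of them.

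**Step 4. Size of the delay.** The longest wait is one listing interval, about 3 months, for an event just after a listing. If events fall evenly over the interval, the mean wait is 3 / 2 = 1.5 months. Follow-up per patient is 30 days (Study subjects), so one interval is about 90 / 30 = 3 times a participant's whole follow-up.

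**Step 5. Patients entered during one interval.** Inputs: 70 per group, hence 140 in total (Sample size). Recruitment time is not in the text shown, so it is varied, with even accrual assumed.

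Randomised per interval = 140 / (years × 4); on PCC = half of that; time of the 70-patient look = half the recruitment time.

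| Recruitment (assumed) | Randomised per 3 months | Of these on PCC | 70-patient look at month |
|---|---|---|---|
| 1 year | 35.0 | 17.5 | 6 |
| 2 years | 17.5 | 8.8 | 12 |
| 3 years | 11.7 | 5.8 | 18 |
| 4 years | 8.8 | 4.4 | 24 |
| 5 years | 7.0 | 3.5 | 30 |

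These are worst-case counts, for an event that just misses a listing.

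**The case against.** The strongest reply is that quarterly listings to an independent DSMB and the ethics committees are a reasoned choice, that close monitoring is delivered at the bedside, and that a full protocol or DSMB charter may add an expedited route. Much of this stands, and it rules out several stronger readings that a reader might infer.

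- **That the reporting rule contradicts the promise of close monitoring.** It does not. The abstract promises to monitor the occurrence of these events, and the schedule of ultrasound, ECG, troponin and examinations does so. It makes no promise about how fast the DSMB is told.
- **That thromboembolism can never be a SUSAR because it is an expected event.** The summary of product characteristics is not shown. The article says that it describes the known and potential risks, but not that it lists thromboembolism. Background says that no thromboembolic events have been reported with the manufacturer's PCC since 1973, and other sections call the risk theoretical. A suspected case might well be classed as unexpected and take the real-time route.
- **That the site alone decides, while blinded, whether an event is a SUSAR.** The article does not say who judges relatedness or expectedness.
- **That the listings should carry counts by treatment arm.** Listing format and unblinded access are commonly left to a full protocol or charter, so their absence here is no finding. Repeated unblinded looks would also be debatable in themselves.

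What remains is narrower. The article does not merely leave the matter open: it states which events are reported in real time, and serious thromboembolic events are not among them unless fatal or judged SUSARs. The background-morbidity argument does not explain why the event of special interest should depend on that classification.

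**Conclusion.** The point holds in limited form. Under the rule as written, a non-fatal thromboembolic SAE not judged a SUSAR can wait up to about three months before the DSMB sees it. The gap is in reporting, not in detection, and it is not an internal contradiction.

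The three-month figure follows directly from the text. The number of patients treated meanwhile does not: about 4 to 9 on PCC at 2 to 4 years of recruitment, or 3.5 to 17.5 over the full range of 1 to 5 years, all under even accrual. How many events would be affected depends on how they are classified, which the article does not settle. It is a cheap improvement of low to moderate severity.

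**What to change.** In the section on (serious) adverse events and SUSARs:

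1. Add serious thromboembolic events, whatever their expectedness, to the category reported in real time to the Sponsor. The sites of thrombosis that the article already names (hepatic vessel, intracardiac, pulmonary, deep venous) can serve to define them.
2. State that the Sponsor forwards these reports promptly to the DSMB, without the qualifier that now governs onward notification.
3. State that treatment teams, investigators and Sponsor stay blinded in this process.
4. Keep the three-monthly listing for all other SAEs.

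The cost is a change of wording, a few extra expedited reports on events that are already recorded in the CRF, and slightly more administration for the DSMB. The endpoints, the sample size and the interim analysis are unaffected.

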#### Annual safety report

In addition to the expedited reporting of SUSARs, the Sponsor will submit, once a year throughout the clinical trial, a safety report to the accredited MREC, CA, Medicine Evaluation Board and CA of the concerned Member States.

### Ethical considerations

This trial will be conducted according to the principles of the Declaration of Helsinki and according to Good Clinical Practice (GCP) guidelines. The trial has been approved by the Medical Ethical Committee (MEC) of the University Medical Center Groningen (UMCG) for all Dutch participating centers. The trial has to be approved by the MEC of participating centers in other countries before those centers can start with the inclusions. Prior to randomization, written informed consent has to be obtained from all participants.

All participating centers have an insurance policy for patients participating in this trial in their centers, according to the legal requirements in their country and all centers are required to inform the participating patients about the insurance policy.

### Data and material collection

All trial data will be anonymous collected in the Case Record Form (CRF). Patient will be ascribed a unique study number and a unique randomization number. Name, address and date of birth will be stored separately from the trial data. Independent monitoring will be established to ensure that this trial is conducted, recorded and reported in accordance with the protocol and GCP. The Investigators, members of the Health Inspection and members of the Medical Ethical Committee have access to personal data. With informed consent research data will be stored during 15 years. Human material will be stored non-traceable for 15 years, when informed consent is obtained. We expect that the stored material will be very valuable for future research.

## Discussion

Patients with end-stage liver disease have an abnormal hemostatic system which is characterized by reduced plasma levels of both pro- and anticoagulant proteins. This results in a hemostatic balance that is more fragile than in healthy persons, a phenomenon that has been described as the ‘rebalanced hemostatic system’ [1]. This rebalanced, yet more fragile, hemostatic system is compatible with the observed higher incidence of bleeding as well as thromboembolic complications in patients with end-stage liver disease. An additional factor that plays a critical role in the increased bleeding risk in these patients is the presence of portal hypertension. Especially, when patients with cirrhosis require an abdominal surgery, the risk of bleeding during the procedure is related to the increased pressure in the portal vein and the venous splanchnic circulation. Fluid overload and sequestration of volume in the venous circulation may contribute to this component of the increased bleeding tendency in patients with cirrhosis when undergoing surgery. Based on this knowledge a restrictive fluid infusion and blood product transfusion policy has been propagated in these patients [25-28].

PCC is a low volume plasma product that contains high concentrations of both pro- and anticoagulant proteins. In contrast to the traditional infusion of FFP to stimulate coagulation in cirrhotic patients, PCC does not add to the intravascular volume and therefore may be, theoretically, more effective in reducing bleeding complications than FFP infusion. The efficacy and safety of PCC in patients with liver cirrhosis requiring major abdominal surgery, however, has never been demonstrated.

A potential side effect of PCC in patients with cirrhosis may be a higher risk of thromboembolic complications. Thromboembolic complications are not infrequent after OLT and when thrombosis occurs in one of the hepatic vessels, this may lead to graft loss. In addition, patients undergoing OLT are at increased risk of developing central venous thromboembolic complications such as intracardiac thrombosis or pulmonary embolism [43]. The PCC we are going to use in our study is commercially available under the product name Cofact®. The efficacy and safety of Cofac® has been evaluated in several clinical studies and so far there has been no indication of an increased risk of tromboembolic events in participating patients [42,44-46]. However, most of these trials have been conducted in patients using vitamin K antagonists. There has been no trial reporting the use of Cofact® in cirrhotic patients. With regards to the nature of the product, the disturbed hemostasis in cirrhotic patients and the hemostatic disturbances caused by the OLT, we decided that thromboembolic complications will be an important secondary and safety endpoint in this trial.

For our primary endpoint we have chosen the number of transfused units of RBC. Blood loss will be registered as well, but should be considered as less stable parameter as blood loss will be mixed with ongoing loss of ascites.

The dosage of PCC will be determined for each individual patient, based on preoperative bodyweight and INR. We will not try to subtract preexisting ascites from the measured bodyweight as this will be hard to quantify preoperatively. Moreover, it can be expected that a proportion of the PCC will be lost through diffusion into the ascites. The current dosages of Cofact® are based on calculations used for the correction of a prolonged INR in patients receiving vitamin K antagonist therapy. We do not know yet whether the same dosing scheme can be used for patients with a prolonged INR due to liver insufficiency. To confirm adequate dosing of PCC we will perform a interim analysis of the INR measurements in stored plasma sampled taken in each patient 30 minutes after the administration of the trial medication. These INR measurements will be performed by a central laboratory and data will be analyzed by an independent researcher who is not involved in conduction of the study. The blinded INR measurements will be used to assess whether the dosing is sufficient or needs adjusting. No INR measurements will be performed during OLT by the local teams.

During the conduction of this trial the surgical and anesthesiological team, treating physicians, and all investigators have to remain blinded for the intervention. This raised a few practical challenges which will be dealt with by a standardized procedure for preparation of the study medication. On-site training and instructions will be given to the local investigators and teams to ensure adequate compliance with these procedures. One of the challenges we have dealt with is that PCC has a light blue color when dissolved. This blue color is visible when the product is in a syringe, but not when flushed through an infusion line. To keep the local teams blinded for the medication group we have chosen to wrap the syringes in aluminum foil before presenting them to the anaesthesiologist.

Randomization and preparation of the study medication will be performed outside the operating theatre by an independent assistant who is not further involved in the patient’s care or in the conduct of this trial.

## Abbreviations

AE: Adverse Event; CRF: Case Record Form; DSMB: Data Safety Monitoring Board; GCP: Good Clinical Practice; IMP: Investigational Medicinal Product In this study the IMP is either Prothrombin Complex Concentrate (Cofact®/ PPSB-D) or placebo (NaCl 0.9%); INR: International Normalized Ratio; LMWH: Low Molecular Weight Heparin; OLT: Orthotopic Liver Transplantation; PCC: Prothrombin Complex Concentrate; PT: Prothrombin Time; MEC: Medical Ethics Committee; (S)AE: (Serious) Adverse Event; SPC: Summary of Product Characteristics; Sponsor: The Sponsor is the party that commissions the organization or performance of the research, for example a pharmaceutical Company, academic hospital, scientific organization or Investigator. A party that provides funding for a study but does not commission it is not regarded as the Sponsor, but referred to as a subsidizing party, in this case the Company; SUSAR: Suspected Unexpected Serious Adverse Reaction; WMO: Medical-Scientific Research Act (in Dutch: Wet Medisch-Wetenschappelijk Onderzoek).
